### Magnetic resonance imaging and analysis

3.5

All study patients will undergo two fMRI examinations for three‐dimensional (3D) magnetization‐prepared rapid gradient‐echo (MPRAGE) imaging, rsFC assessment, and diffusion‐weighted imaging (DWI) using an advanced GE Signa HDx 3.0T MR system (GE Healthcare) in accordance with the recommendation of the Human Connectome Project for mapping neural connections of the human brain (http://www.neuroscienceblueprint.nih.gov/connectome/). Two hours before the initiation of ketamine infusion, patients in the daytime ketamine administration group will be scheduled for baseline fMRI examination at 9 a.m., and those in the nighttime ketamine administration group will undergo baseline fMRI examinations at 4 p.m. Twenty‐four hours after baseline fMRI, repeat fMRI examinations will be performed for patients in these two groups (Figure 1).

Functional magnetic resonance imaging examinations will be performed using the following parameters. For T1‐weighted 3D MPRAGE structural imaging of the whole brain, 128‐layer sagittal scanning will be carried out for 4 min using the following parameters: 1.33 mm thickness, 0‐mm interval, 256 × 192 in‐layer resolution, 2,530‐ms repetition time (TR), 3.39‐ms echo time (TE), 7° flip angle (FA), and 256 × 256 mm^2^ field of view (FOV). For rsFC assessment, 33‐layer axial imaging will be undertaken for 10 min with the following parameters: 3 mm thickness, 0‐mm interval, 64 × 64 in‐layer resolution, 2,000‐ms TR, 30‐ms TE, 90° FA, and 220 × 220‐mm^2^ FOV. For the digital trunk interface (DTI) module, the following parameters will be used: 70 layers with 2 mm thickness, 0‐mm interval, 7,100/61‐ms TR/TE, 256 × 256‐mm^2^ FOV, and 128 × 128 matrix. The gradient direction will be set to 64 (*b* = 1,000, *b*0 image = 10, NEX = 1). For the diffusion kurtosis imaging (DKI) module, a 2D multislice single‐shot spin‐echo echo‐planar‐imaging sequence will be used with 48 layers of 3 mm thickness, 0‐mm interval, 5,800/77‐ms TR/TE, 90° FA, 256 × 256 mm^2^ FOV, and 128 × 128 matrix. The gradient directions will be set to 25 (*b* = 1,000) and 25 (*b* = 2,000), with *b*0 image = 10 and NEX = 1. For magnetic resonance spectrometry, a single voxel spectrum will be located in the ACC; the TE will be set to 2,000 ms.

In MRI examination, sagittal 3D T1‐weighted images will be acquired using the following parameters: 188 sagittal slices, 1 mm slice thickness, no gap, 8.2‐ms TR, 3.2‐ms TE, 450‐ms inversion time (TI), 12° FA, 256 × 256 mm^2^ FOV, and 256 × 256 matrix. Resting‐state fMRI data will be acquired using a single‐short gradient‐echo echo‐planar‐imaging sequence with the following parameters: 32 interleaved transverse slices, 4 mm slice thickness, 0.5‐mm gap, 2,000/45‐ms TR/TE, 90° FA, 220 × 220 mm^2^ FOV, 64 × 64 matrix, and 180 volumes. For analysis of the brain white matter, a single‐shot spin‐echo‐planar‐imaging sequence will be used with three diffusion weightings (*b* = 1,000, 1,500, and 2,000 s/mm^2^), 30 noncollinear directions, and five *b* = 0 s/mm^2^ volumes (13,000‐ms TR, 86.1‐ms TE, 1.88 × 1.88 × 2.50‐mm^3^ voxel size). The diffusion gradient length (*δ*) and spacing (Δ) will be held constant (*δ*/Δ = 35.1/44.7 ms). Raw images will be denoised, corrected for Gibbs ringing, and corrected for eddy currents and motion using the *eddy* tool in the FMRIB Software Library (version 6.0; Analysis Group, FMRIB). DTI and DKI parameters will be calculated using weighted linear least‐squares estimation (https://github.com/NYU-DiffusionMRI/Diffusion-Kurtosis-Imaging).

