## METHODS AND STUDY DESIGN

3

This study protocol is designed to test the main hypothesis that ketamine could rapidly reverse depression‐ and stress‐associated synaptic losses or deficits in resting‐state functional connectivity (rsFC) and that this action could be affected by circadian rhythms, in patients with treatment‐resistant depression. The design of this study is illustrated in Figure 1.

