### Randomization and treatment

3.2

R/S‐ketamine hydrochloride, sold under the brand name Ketalar (Pfizer Pharmaceuticals), will be used as the study drug. A total of 600 adult patients with treatment‐resistant depression will be enrolled in this study. Randomization and stratification of the study patients will be carried out using the Randomization in Treatment Arms software (Evident). The patients will be assigned to the following three groups (200 per group): placebo, daytime ketamine administration, and nighttime ketamine administration. Patients in the ketamine groups will be given ketamine infusions at a dose of 0.5 mg/kg (R/S‐ketamine hydrochloride diluted in saline, administered slowly by i.v. pump for >40 min) in the morning and at night, respectively (Berman et al., 2000; Zarate et al., 2006); patients in the placebo group will receive matching saline infusions (Figure 1). These patients will receive two infusions per week for 24 weeks (Singh et al., 2016). Treatments will be administered in private rooms at the Mental Health Teaching Hospital affiliated with Tianjin Medical University.

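### Section 3.5 promises two fMRI examinations to every patient but times the baseline and repeat scans only for the two ketamine groups, so placebo scanning must be reconciled before the connectivity change can be read as a drug effect

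*Protocol article*

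**What the plan says.** Section 3.2 of the protocol article randomises patients to three arms of 200: "placebo, daytime ketamine administration, and nighttime ketamine administration". It adds that "patients in the placebo group will receive matching saline infusions" but gives no clock time for them. Section 4.1 names saline as the control for the two ketamine interventions.

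The opening paragraph of section 3 states the main hypothesis, which includes reversal by ketamine of "deficits in resting‐state functional connectivity (rsFC) and that this action could be affected by circadian rhythms".

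Section 3.5 covers the scans that bear on that hypothesis:

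- It begins with a commitment for the whole trial: "All study patients will undergo two fMRI examinations".
- It sets each ketamine group's baseline scan two hours ahead of its infusion. For one group it says that "patients in the daytime ketamine administration group will be scheduled for baseline fMRI examination at 9 a.m"; the other ketamine group has its baseline slot at 4 p.m.
- It places the second scan 24 hours after the first and says that "repeat fMRI examinations will be performed for patients in these two groups", citing Figure 1.

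The text gives no baseline time and no repeat scan to the placebo group. Section 3.11 states a ketamine versus placebo contrast for the MADRS and none for imaging.

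**The concern.** The commitment to all patients and the schedule for two groups stand in the same paragraph and cannot both be carried out. A site that works from the schedule would scan ketamine patients only.

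In that case the rsFC part of the main hypothesis would rest on change within ketamine-treated patients. A second scan a day after the first can differ for reasons unrelated to the drug, such as familiarity with the scanner or the expectation of benefit after an infusion. Without a placebo repeat scan, these cannot be subtracted. MRI is also the only imaging that could supply a placebo contrast, because section 3.6 draws the PET subset from the ketamine groups alone.

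A scan that is not done before the first infusion and 24 hours later cannot be recovered, so the text needs settling before enrolment.

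**Working it through.** **1. The statements side by side.**

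| | Opening sentence of section 3.5 | Schedule in section 3.5 |
|---|---|---|
| Daytime ketamine | two scans | 9 a.m., repeat 24 h later |
| Nighttime ketamine | two scans | 4 p.m., repeat 24 h later |
| Placebo | two scans | nothing stated |

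**2. Scan counts** (200 per group, section 3.2).

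- Opening sentence: 3 × 200 × 2 = 1,200 examinations.
- Schedule: 2 × 200 × 2 = 800 examinations.
- Difference: 400 examinations, all in the placebo group.

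Section 3.8 gives a total of 800 patients rather than 600. I use section 3.2 because it alone gives group sizes. The mismatch between the two sentences does not depend on the total.

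**3. Clock times.** The abstract puts the infusions at 11 a.m. and 6 p.m. Two hours earlier is 9 a.m. and 4 p.m., as section 3.5 says. The repeat scan falls 24 − 2 = 22 hours after the infusion starts. No placebo scan time can be derived in this way, because no clock time is given for the saline infusion.

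**4. Time of day.** Each patient is scanned twice at the same hour, so any constant effect of clock hour cancels in the within-patient change. What could remain is an interaction, where the retest change itself differs between a 9 a.m. pair and a 4 p.m. pair. The documents give no size for this.

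**5. How easily a non-drug shift would be called significant.** The documents give no retest figure and state no imaging test, so this step is an illustration. Assume a two-sided paired test at 0.05 on the 400 ketamine patients and a drug-unrelated shift of d SDs of change. The noncentrality is d × √400 = 20d, the critical value is about 1.966, and the chance of significance is about Φ(20d − 1.966).

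| Assumed d | 20d | Chance of significance |
|---|---|---|
| 0.10 | 2.0 | 0.51 |
| 0.15 | 3.0 | 0.85 |
| 0.20 | 4.0 | 0.98 |

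At d = 0.20, 15% dropout (n = 340) gives about 0.96, and a single ketamine arm (n = 200) gives about 0.80.

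**6. The same shift with a placebo group.** If the shift is equal in all arms, its expected contribution to the ketamine minus placebo difference is d − d = 0, and the chance of a false positive returns to 0.05. The standard error of that difference, in SDs of change, is √(1/400 + 1/200) = 0.087.

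**The case against.** The strongest reply is that the article never says placebo patients go unscanned. Its opening sentence commits to scanning them. Where imaging is meant for ketamine arms only, as with PET in section 3.6, the article says so openly. The schedule is anchored to the ketamine infusion, which may explain why only the ketamine groups are named. The sentence on the repeat scan cites Figure 1, which is not shown, and a full protocol may hold the placebo visits. All of this stands. A reader might infer that the connectivity hypothesis has no placebo comparison; the documents do not support that. They support only that placebo scans are promised and then left out of the written schedule. The PET section cuts both ways, though: it shows that ketamine-only imaging is a choice made in this trial, so the restriction cannot be dismissed as a slip.

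A reader might also infer that time of day confounds the 24-hour change. It does not as a main effect, since both scans fall at the same hour; only the interaction in step 4 of the working is open.

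The figure of 0.98 should not be quoted alone. It needs an assumed shift of 0.2 SD and a pooled pre-post test that the article does not state. At half that shift the chance is 0.51.

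Finally, the primary outcome, change in MADRS, is unaffected.

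**Conclusion.** The point holds as an internal contradiction with a conditional consequence. Section 3.5 promises two fMRI examinations to all patients and schedules them for two arms of three, leaving 400 of 1,200 examinations without a stated time. If sites follow the schedule as worded, and Figure 1 does not say otherwise, the 24-hour rsFC change has no saline control and cannot be attributed to ketamine. Large pre-post samples would make even modest non-drug shifts likely to reach significance, but how likely depends on an assumed shift (0.51 to 0.98 over the range 0.1 to 0.2 SD).

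It should be corrected before enrolment. It is cheap to settle now, and the missing scans could not be obtained afterwards.

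**What to change.** Reconcile the two sentences in section 3.5, and check Figure 1 against the result:

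- Extend the baseline and 24-hour repeat scans to all three groups.
- Time placebo scans relative to the placebo infusion in the same way as in the ketamine groups, and state the hours. Where the sponsor's timing of placebo infusions allows, cover both scan hours. This should not be read as setting infusion times, which the sponsor must state separately.
- Base the rsFC claim on ketamine versus placebo 24-hour change, adjusted for baseline and scan hour. In the ketamine groups, scan hour and treatment arm coincide. If placebo patients are scanned at one hour only, they therefore provide a same-hour control for just one ketamine arm, and the text should say so.

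If the sponsor does intend to scan ketamine patients only, the opening sentence must change instead, and the rsFC result should be described as an uncontrolled pre-post change.

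The cost is protocol wording and visit planning. The extension needs 400 examinations more than the present schedule lists, but none beyond the two per patient already promised.

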### PET imaging and analysis

3.6

For PET imaging, 40 patients will be randomly selected from the daytime and nighttime ketamine administration groups (20 per group) to undergo PET scans using the ^11^C‐UCB‐J PET ligand at baseline and upon completion of the 24‐week treatment period. This subset of patients will be included in consideration of the difficulties involved in brain PET, including poor patient compliance and high cost (Rausch et al., 2017; Thompson et al., 2016). In brief, PET imaging will be performed using a high‐resolution research tomography (GE Health Care) with a reconstructed image resolution of nearly 3 mm, as described previously (Finnema et al., 2018; Nabulsi et al., 2016). These patients will also undergo T1‐weighted MRI imaging in a 3‐T whole‐body scanner (GE HealthCare) at the same timepoints for coregistration with the PET images.

### Blood sampling and molecular biological studies

3.7

Peripheral blood samples (5 ml) will be collected from all patients at baseline and upon treatment completion for the quantification of ketamine levels and molecular biological studies. The blood samples will be centrifuged at 5,000 *g* for 10 min, and the serum samples will be stored at −80°C in a freezer. An enzyme‐linked immunosorbent assay kit (Sigma‐Aldrich) will be used for the measurement of serum BDNF levels on a SpectraMax M5 microplate reader (Molecular Devices) at a wavelength of 450 nm. All samples will be measured in triplicate. Genomic DNA will be extracted from the blood samples and used for subsequent genetic polymorphism genotyping with two genes of interest (Homer1 and BDNF), performed at the molecular core laboratory of Tianjin Medical University. Researchers blinded to the clinical data will perform the genotyping of Homer1 at rs7713917 (the A allele indicates a higher risk of dysregulation of cognitive and motivational processes through effects on prefrontal activity during anticipation of reward), rs2290639 (the AA homozygote was associated significantly with suicide attempts in Chinese patients in Hong Kong), and rs60029291 (the T allele was associated with MDD and suicide attempts in Chinese patients), as described previously (Serchov et al., 2015).

### Sample size determination and power analysis

3.8

The effective sample size has been estimated using G‐Power analysis according to the G * Power 3.1 manual, released in March 2017 (http://www.gpower.hhu.de/en.html). Assuming a 15% dropout rate in each group and to observe significant effects with an *α* value of 0.05 and statistical power of 0.8, a total of 800 patients with treatment‐resistant depression will be enrolled in the randomized, double‐blinded control study.

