### Limitations of this study protocol

4.2

Despite the obvious strengths of this study, some potential limitations of our study protocol should be noted. First, we recognize that this entire pilot study will be conducted at a single center and that selection bias may be a weakness. In addition, our hospital‐based enrollment method could affect our findings. Second, although the sample size was calculated to generate sufficient power for the assessment of differences in intervention efficacy among study groups, it may not be large enough to enable analysis of subgroups, such as those defined by sex and genetic variants. Third, although we do not anticipate this to be the case, it is possible that differences in certain patient characteristics could affect the outcomes. Another weakness of this protocol could be that we will not be able to stratify randomization by sex.

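### Section 3.2 enrols 600 patients and section 3.8 enrols 800; the 15% dropout does not reconcile them, and the only power statement belongs to the 800

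*Protocol article*

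**What the plan says.** Section 3.2 (Randomization and treatment) states: "A total of 600 adult patients with treatment‐resistant depression will be enrolled in this study". The allocation follows: "The patients will be assigned to the following three groups (200 per group): placebo, daytime ketamine administration, and nighttime ketamine administration". The total and the per-arm numbers agree with each other.

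Section 3.8 (Sample size determination and power analysis) reports a G*Power calculation. Its stated inputs are dropout ("Assuming a 15% dropout rate in each group") and an alpha "value of 0.05 and statistical power of 0.8". Its result is that "a total of 800 patients with treatment‐resistant depression will be enrolled in the randomized, double‐blinded control study". It gives no per-arm number.

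Section 3.11 (Data handling and statistical methods) plans a one-way ANOVA of MADRS scores over the groups, then post hoc tests of ketamine against placebo and of daytime against nighttime ketamine. Section 4.2 (Limitations) relies on the calculation: "the sample size was calculated to generate sufficient power for the assessment of differences in intervention efficacy among study groups".

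**The concern.** Both sections use the future tense of enrolment for the same trial, and the totals differ by 200 patients, a quarter of the larger one. The power statement is tied to one total and the allocation to the other. A reader therefore cannot tell which design the 80% describes, or at what count recruitment ends.

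At stake is the assurance in section 4.2. If the calculation really needs 800, the three arms of 200 fall short of the stated power. If it needs 600, the sample-size section carries a wrong enrolment figure. In either case the article as written does not support a power claim for the trial that it describes in section 3.2.

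**Working it through.** **Inputs from the article.** Enrolled: 600 = 3 x 200 (section 3.2) or 800 (section 3.8). Dropout 15% per group, alpha 0.05, power 0.80 (section 3.8). One-way ANOVA, then two post hoc comparisons (section 3.11). Two-sided testing is my assumption for the pairwise contrasts, because the article does not state sidedness.

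**Step 1. Can the 800 be reproduced?** No. The article gives no effect size, SD or test for the G*Power run, so the figure cannot be rebuilt from its stated inputs.

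**Step 2. Does dropout connect the totals?**

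| Check | Result | Needed |
|---|---|---|
| 600 / (1 - 0.15) | 706 | 800 |
| 600 x 1.15 | 690 | 800 |
| 800 x (1 - 0.15) | 680 | 600 |
| Loss needed to go from 800 to 600: 1 - 600/800 | 25% | 15% |
| 800 / 3 | 266.7 per arm | 200 |

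None of these works. The article mentions no screening allowance or second cohort. The PET subset of 40 (section 3.6) is drawn from within the ketamine arms and adds nobody.

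**Step 3. What follows if 800 is the calculated number?** Assume that 800 enrolled, or 800 x 0.85 = 680 evaluable in three equal arms (226.7 each), gives exactly 80% power. Solve for the effect, then apply it to 600 x 0.85 = 510 evaluable (170 per arm).

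- *Three-group ANOVA.* Power = P(F' > F crit), where F' is noncentral F with 2 and N - 3 degrees of freedom and noncentrality N f². At N = 680, 80% power gives f = 0.119. The noncentrality falls from 680 x 0.1193² = 9.68 to 510 x 0.1193² = 7.26, and power at N = 510 is 67.0%.
- *One pairwise contrast, two-sided 0.05.* Power comes from the noncentral t with noncentrality d √(n/2). At n = 226.7, 80% power gives d = 0.264. At n = 170 the same d has 67.9% power.
- *Same contrast with smaller alpha.* Repeating both steps gives about 66.5% at alpha 0.025 and 65.7% at 0.0167.
- *If the 600 meant completers,* although the text says enrolled, ANOVA power for f = 0.119 would be 74.5%.

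**Step 4. What follows if 600 is the calculated number?** As an illustration, assume a pairwise d = 0.30 at two-sided 0.05. Then n = 2(1.96 + 0.8416)²/0.30² = 174.4, so 175 per arm, 525 in three arms, and 525/0.85 = 618 enrolled. That is 3% above 600. The article does not state this effect. The example shows only that a calculation leading to about 600 is plausible.

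**Step 5. What can 600 enrolled detect with 80% power?** With 510 evaluable, 170 per arm:

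| Test | Detectable effect |
|---|---|
| Three-group ANOVA, 0.05 | f = 0.138 |
| One pairwise contrast, two-sided 0.05, unadjusted | d = 0.305 |
| One pairwise contrast, two-sided 0.025 (alpha split over two comparisons) | d = 0.336 |

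The f and the d values are thresholds for different tests, not one effect on two scales. If the third arm lies midway between two arms that differ by d = 0.305, then f = √(2 x 0.1525²/3) = 0.125, not 0.138.

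**The case against.** The strongest reply is that this is one wrong number. Section 3.2 gives 600 with arms that add up, 800 appears only once, the article calls the study a pilot, and a modest assumed effect leads to about 618. On that view the trial may be adequately powered at 600 and nothing is lost. This stands as far as it goes: the article cannot rule it out. It does not remove the contradiction, because the sample-size section would then state a wrong enrolment total, and its power statement would still be attached to that total.

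Some stronger readings are tempting but not supported:

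- *That the trial is underpowered at 67-68%.* This holds only if 800 was the calculated number and gives exactly 80% power in three equal arms. The article shows neither.
- *That the power claim matches neither total.* Section 3.8 attaches it to 800.
- *That 800 points to a fourth arm of 200.* The abstract and sections 3.2 and 3.9 describe three groups.
- *That the daytime-nighttime comparison suffers most.* All arms are equal, so every pair has the same precision, and no expected effect is given for any contrast.
- *That the absent effect size is a separate defect.* A condensed article may leave it to the full protocol. Here it matters only because it prevents a reader from settling which total is right.

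**Conclusion.** The contradiction is real and must be resolved. The two totals differ by 200 patients, the stated dropout does not bridge them, and no other text links them. The assurance of sufficient power in section 4.2 is therefore unsupported for three arms of 200.

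The cost in power is conditional. If 800 was calculated for 80% power, 600 enrolled gives about 67-68% for the same effect, or slightly less with adjusted alpha. If 600 was calculated, the loss is zero and the 800 is an error of text. The contradiction itself rests on no assumption. The power figures assume 15% dropout, equal arms and two-sided pairwise tests.

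**What to change.** Use one enrolment total, with per-arm numbers, in sections 3.2 and 3.8. State the 80% power for that total together with the effect size, the SD, the test and the alpha it was calculated for, and bring the sentence in section 4.2 into line.

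If the design stays at 3 x 200, give 600 enrolled and 510 evaluable after 15% dropout (170 per arm), and state the detectable effect for the analysis actually planned: f = 0.138 for the three-group ANOVA, or d = 0.305 for one unadjusted pairwise contrast. The pairwise figure should not be offered alone, because section 3.11 plans two post hoc comparisons; with alpha split over both it is about d = 0.336. If 800 was calculated for a specific effect, state that effect and the roughly 67-68% power that 600 provides for it.

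The cost is wording in three sections. Keeping 600 needs no extra patients. The stated power or detectable effect becomes less favourable only if 800 was the calculated number.

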**Methods/Study Design:**

In this clinical study, adults (aged 18–65 years) with treatment‐resistant depression will be randomized to intravenous administration of placebo (control group) or ketamine (0.5 mg/kg body weight) at 11 a.m. (daytime group), or 6 p.m. (nighttime group) for 24 weeks. The primary outcome will be the change from baseline to 24 weeks in the total Montgomery‐Asberg Depression Rating Scale score. Brain imaging, sleep, and genetic studies, including functional magnetic resonance imaging, positron emission tomography, polysomnography, and genetic analyses, will be performed to examine whether and how ketamine can rapidly reverse deficits in synaptic function and to identify objective markers for the assessment of ketamine infusion therapy for treatment‐resistant depression.

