## STUDY OBJECTIVES

2

This study protocol is designed to examine the mechanisms underlying the rapid and sustained antidepressant actions of ketamine in humans and to test the central hypothesis that ketamine could rapidly reverse depression‐ and stress‐associated synaptic deficits in patients with treatment‐resistant depression, using brain imaging. In addition, this clinical study will be, to our knowledge, the first to prospectively assess the hypothesis that day and night administrations of ketamine would result in different antidepressant actions. We plan to test the main hypothesis and, thereby, to meet the study objective, by pursuing the following specific aims and conducting the proposed studies in patients with treatment‐resistant or treatment‐refractory depression. The long‐term goal of our ongoing research program is to gain neurobiological knowledge of how depression is formed, and how it can be cured through the translation of scientific findings into new efficacious therapeutic approaches.

Specific aim #1: To determine the optimal timing of ketamine infusion therapy for treatment‐resistant depression.
Working hypothesis 1: We hypothesize that day and night administrations of ketamine will have different effects on the efficacy of ketamine for treatment‐resistant depression.Working hypothesis 2: We hypothesize that ketamine administered at night will work better than ketamine administered during the day.

Specific aim #2: To determine whether and how ketamine can rapidly reverse deficits in synaptic function, particularly volumetric abnormalities in the PFC and hippocampus, in patients with treatment‐resistant depression.

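### The protocol claims double-blinding without limit, but as described patients know their infusion hour, so the day-versus-night MADRS comparison behind Specific aim #1 is not patient-blind

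*Protocol article*

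**What the plan says.** Section 3.8 (sample size) gives a total of 800 patients who "will be enrolled in the randomized, double‐blinded control study". This is the article's only statement of the trial's blinding, and it carries no qualification. The abstract does not repeat it.

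The abstract sets the ketamine infusions "at 11 a.m. (daytime group), or 6 p.m. (nighttime group) for 24 weeks". Section 3.2 gives both ketamine arms the same drug at the same dose, "in the morning and at night, respectively". On the control arm it says that "patients in the placebo group will receive matching saline infusions", without giving their hour in the text. On frequency it says: "These patients will receive two infusions per week for 24 weeks".

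Section 2 makes the timing of infusion Specific aim #1. Its first working hypothesis is that day and night differ. Its second is directional: "We hypothesize that ketamine administered at night will work better than ketamine administered during the day". Section 3.11 names daytime versus nighttime as a post hoc comparison after the ANOVA of MADRS scores.

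Section 3.5 schedules the daytime arm's baseline fMRI at 9 a.m., while "those in the nighttime ketamine administration group will undergo baseline fMRI examinations at 4 p.m". The repeat scan follows 24 hours later in each arm.

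**The concern.** Between the two ketamine arms, the clock hour is the allocation. A patient who comes for infusion at 11 a.m. or at 6 p.m. knows it, and so does whoever runs the infusion. A double-blind claim that covers the whole trial therefore covers one comparison for which, on the described procedures, it is not true.

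The comparison matters. It answers the first specific aim, the article's conclusions present it as the novel element, and section 4.1 expects it to influence practice, patient choice and insurance policy. The primary outcome is a symptom rating that includes reported sadness, inner tension and pessimistic thoughts, so it depends on what patients say and how a clinician judges it. If patients or raters come to share the investigators' expectation, some or all of an observed advantage for night could be expectancy. A reader who relies on the double-blind label would not consider that.

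**Working it through.** **Step 1. Set the statements side by side.**

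| Feature | Daytime ketamine | Nighttime ketamine | Source |
|---|---|---|---|
| Drug and dose | same | same | 3.2 |
| Infusion hour | 11 a.m. | 6 p.m. | Abstract |
| Infusion at the other hour | none described | none described | 3.2 |
| Baseline fMRI hour | 9 a.m. | 4 p.m. | 3.5 |
| Blinding label | double-blinded, no limit | double-blinded, no limit | 3.8 |

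Planned infusions per patient: 2 per week × 24 weeks = 48. The allocation is visible to the patient at each one. The label and the described delivery cannot both hold for this contrast. This step needs no assumption about effect size or variance.

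**Step 2. What the label can cover.** Saline that matches ketamine, given at the same hour, can be double-blind for drug. Whether it is so here depends on when placebo is infused, which the text does not state. If all placebo infusions were at one hour, a patient infused at the other hour could infer that the infusion was ketamine.

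**Step 3. The plan's own figure.** The 800 in section 3.8 cannot be reproduced, because no effect size or SD is given. Section 3.2 gives 600 (200 per group). That conflict is a separate matter, so both totals are carried here. With 15% dropout and equal allocation:

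- 600 × 0.85 / 3 = 170 per arm
- 800 × 0.85 / 3 = 226.7, about 227 per arm

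Difference detectable with 80% power at two-sided 5% for one pairwise contrast: (1.96 + 0.84) × √(2/n).

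- n = 170: 0.304 SD, which is 2.4 to 3.6 MADRS points for an assumed SD of 8 to 12
- n = 226.7: 0.263 SD

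**Step 4. Illustration of bias.** Assume no true day-night difference, an expectancy bias of b SD units, and an unadjusted two-sided 5% test. With δ = b/√(2/n), the rejection rate is 1 − Φ(1.96 − δ) + Φ(−1.96 − δ).

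| b (assumed) | n = 170: δ | rate | n = 226.7: δ | rate |
|---|---|---|---|---|
| 0.1 SD | 0.92 | 15% | 1.06 | 19% |
| 0.2 SD | 1.84 | 45% | 2.13 | 57% |

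For an SD of 10, these shifts are 1 and 2 points. Holding the shift at 1 to 2 points and letting the SD run from 8 to 12 (b from 1/12 = 0.083 to 2/8 = 0.25) gives about 12% to 63% with 170 per arm. None of these shifts or SDs comes from the documents.

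**The case against.** The strongest reply is that the double-blind label is naturally read as ketamine versus matching saline, that it appears once in a condensed article, and that a fuller protocol may say who is blinded. The reading is fair, and it is the limit that the text should state. It does not remove the problem: naming blinded raters elsewhere would still leave patients aware of their own hour, and the timing comparison is a declared aim.

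Several stronger readings are tempting but unsupported:

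- **That infusion hour cannot be masked.** A dummy infusion at the other hour could hide which infusion is active. The text describes none, and Figure 1 is not shown. The supportable statement is that no masking of hour is described.
- **That MADRS raters are unblinded.** The article neither says that they know the hour nor that infusion staff do the rating. Only the genotyping researchers are explicitly described as blinded, but silence in an article is not evidence about the other staff.
- **That patients are told night is better.** Section 3.1 says that they are informed about the background and procedures. The consent material is not at hand, and the first hypothesis under the same aim has no direction.
- **That all imaging and sleep readings reveal the arm.** Arm-specific hours are stated for fMRI only, not for PET or polysomnography, and nothing says that analysts see acquisition times.
- **That the error rate is inflated by a known amount.** The bias sizes are assumed, and section 3.11 does not name the post hoc procedure.

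**Conclusion.** The concern holds in a limited form. The unqualified claim in section 3.8 conflicts with the delivery described in the abstract and section 3.2, so the day-versus-night MADRS contrast is not patient-blind as written. Whether bias follows, and how much, depends on what patients and raters believe, which the documents do not show. The rates in step 4 show only that a modest expectancy effect, smaller than the difference the trial could detect with 80% power, could matter at either stated sample size. The finding does not rest on them.

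The ketamine-versus-saline comparison is not shown to be unblinded. Its status depends on the placebo hours, which need to be confirmed. The trial can proceed, but the claim should be corrected and the inexpensive protections put in place, because they limit both the bias and what the timing result can be said to show.

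**What to change.** 1. In sections 3.2 and 3.8, limit the double-blind claim to ketamine versus saline, after confirming that the hours of the placebo infusions support it. State that infusion hour is known to patients and infusion staff. If an undescribed procedure does mask the hour, describe it instead.
2. Present the two hours neutrally in patient information, and keep the prediction that night is better out of material seen by patients and raters.
3. Have the existing MADRS raters kept unaware of infusion hour and arm, and say so.
4. Remove acquisition clock times from the fMRI files given to analysts.
5. Report the day-versus-night MADRS result as not patient-blind.

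The cost is wording in the protocol and patient information, an instruction to raters and patients not to discuss the infusion hour, and a file-preparation step for fMRI. No dose, infusion schedule or visit changes. The downside is a less favourable blinding claim for the timing contrast. Items 2 and 3 reduce the scope for bias. Items 1 and 5 remove none, but they let readers weigh the result correctly.
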